### Summary of aims

1.1

The primary aim is to establish the feasibility of delivering a virtual exercise intervention in community-dwelling individuals with mTBI, including assessment of recruitment rates, adherence, retention, and safety parameters. The secondary aim establishes precision around the mean and variance [64] of a symptom-guided aerobic exercise intervention to change cognitive function and metrics of brain structure and function following recent (within 1-year of injury) mTBI. Two exploratory aims will investigate: (1) the precision around the mean and variance of aerobic exercise's effect on cognitive function; and (2) the precision around the mean and variance of aerobic exercise's effect on neuroimaging measures of brain structure, function, connectivity, and perfusion. A final exploratory aim is to measure changes in objectively measured daily physical activity and sedentary behaviors measured three times across the intervention period and their associations with neurological and cognitive outcomes.

## Methods

2

### Study design

2.1

The current study is a stratified block two-arm pilot randomized controlled trial design with multiple complementary objectives. After reading and signing informed consent, recruited participants are randomized into either an aerobic exercise (intervention) or balance exercise group (control) with a ratio of 1:1 (Fig. 1). All participants are informed about the randomization but blinded to their group assignment, meaning they are unaware which group is intended to be intervention. Participants are informed that the study aims to examine whether a 12-week exercise program promotes brain health and cognition after an mTBI. However, it is not possible to blind experimenters, as they lead the intervention sessions and give instructions during the assessments. The randomization scheme is prepared by the Tufts Clinical and Translational Science Institute Group using a permuted block method with random blocks of 4 and 6. Randomized block design is used to increase experimental precision and reduce the impact of unwanted variability (nuisance factors) by grouping similar subjects or experimental units into blocks before randomly assigning treatments within each block. This trial is registered on clinicaltrials.gov under identifier NCT06494592. This study received ethical approval from Northeastern University Institutional Review Board (IRB).

**Fig. 1 fig1:**
[figure not shown]
Overall Study Design. Baseline is followed by 12-week intervention period with actigraphy at Week 1, Week 6, and Week 12. After completion, an endpoint visit is conducted.

### Eligibility

2.2

The eligibility criteria are designed to recruit individuals who have a clinical diagnosis of mTBI within the last previous year and can safely engage in aerobic exercise (Table 1).

### Recruitment

2.3

We will recruit participants until a final sample of 24 has completed all 12 weeks. Adults aged 18–55 years who have sustained a clinically diagnosed mTBI, confirmed by a neurologist (AS), within the past year are eligible to participate. Complete inclusion and exclusion criteria are detailed in Table 1. To ensure representative findings, we will actively recruit a diverse participant population with balanced representation across race, sex, and socioeconomic status. Recruitment strategies include multi-modal advertising approaches, including promotional flyers distributed throughout healthcare facilities, community centers, and university campuses in the greater Boston metropolitan area. Additionally, targeted online recruitment will be conducted through social media platforms (e.g., Facebook) and community-based websites (e.g., Craigslist) to maximize reach across diverse demographic groups. We will also establish partnerships with local healthcare providers, rehabilitation centers, and concussion clinics to facilitate referrals of eligible participants.

### Screening

2.4

Questions about medical history, safety to exercise [65] and MRI Safety are asked in the initial phone screen by research staff. Participants are required to be diagnosed with a mTBI within the last one year, cleared to exercise, and be safe for an MRI scan before enrolling. If participants do not have a clinical diagnosis, our clinician (AS) will evaluate them for mTBI via phone interview and OSU TBI Questionnaire.

### Randomization

2.5

Participants are randomized after the baseline session is complete using a block randomization in block sizes of four and six with equal allocation to each group. Randomization were done in REDcap.

### Cognitive testing

2.6

The cognitive tests were chosen to provide measures of domains with known deficits after a mTBI and which are commonly used in clinical practice, and were administered at baseline and endpoint. Hopkins Verbal Learning Test (HVLT) [66] provides measures of memory, including immediate and delayed recall. Letter [67] and category fluency [68] provides measures of language. The Trail Making Test (TMT) [69] A and B provides measures of processing speed and executive functioning.

### Symptom threshold and cardiorespiratory fitness testing

2.7

We developed an in person hybrid symptom threshold test (similar to the Buffalo concussion treadmill test and others [36,70]) to objectively determine the exercise intensity (and heart rate) at which concussion-associated symptom severity increases beyond baseline levels (defined as an increase of ≥3 units above baseline), and combined sub-maximal cardiorespiratory fitness estimation of VO_2_max (based on the Astrand-Rhyming 6-min protocol [71]) (Fig. 2). Together, these assessments will determine the appropriate intensity for aerobic exercise sessions in the intervention group and provide a pre-post measure of CRF. The complete assessment (administered at baseline and post-intervention) consists of three sequential phases conducted on a cycle ergometer: warm-up, Astrand-Rhyming test [72], and symptom threshold test. Baseline vital signs (heart rate, blood pressure) are recorded during seated rest. Participants complete a graded concussion symptom checklist to establish baseline symptom ratings. Heart rate (Polar H7 chest strap, Polar, Kempele, Finland), ratings of perceived exertion (RPE; Borg scale), and concussion symptoms are assessed every 2 min during all phases using the CIF. During Phase 1 (Warm-up) participants cycle at self-selected resistance and pace for 7 min. Then, Phase II (Astrand Rhyming Test) begins. Participants cycle at 50 revolutions per minute (RPM) at a predetermined workload (calculated in watts based on participant weight) for 6 min. The cycle ergometer automatically calculates workload in watts for subsequent VO_2_max estimation using the Astrand-Rhyming nomogram. The average heart rate during the fifth minute is recorded. The test phase concludes when steady-state heart rate is achieved (defined as heart rate variations ≤10 beats per minute). The steady-state heart rate and workload are used to estimate VO_2_max via nomogram extrapolation. Upon completion of the VO_2_max estimation, participants are instructed to increase their pedal cadence to 60 RPM. Resistance increases every 30 s until one of the following termination criteria is met: increase of ≥3 symptoms above baseline levels, 85 % of age-predicted maximum heart rate or RPE of 18 on the Borg scale, any relative or absolute contraindication to exercise testing. The heart rate at symptom threshold is recorded and used to prescribe aerobic exercise intensity for intervention sessions.

**Fig. 2 fig2:**
[figure not shown]
Boston Exercise Symptom Threshold Test Timeline and decision tree.

### Balance test

2.8

The Balance Error Scoring System (BESS) [73] will be used to evaluate postural stability and administered by trained research staff. The BESS protocol consists of three stance positions performed on two different surfaces (firm and foam), yielding six total testing conditions. The three stance positions include double-limb stance with feet together in a narrow base of support, single-limb stance on the non-dominant leg only, and tandem stance with the non-dominant foot positioned behind the dominant foot in heel-to-toe alignment. Each stance is performed on both a firm surface (standard flat ground) and a foam surface (medium-density foam pad). Each of the six conditions is performed for 20 s with eyes closed while a trained evaluator observes and scores each trial by counting balance errors. Balance errors are defined as opening eyes, lifting hands off hips, stepping, stumbling, or falling, lifting the forefoot or heel off the ground, or hip abduction or flexion greater than 30°.

### Brain magnetic resonance imaging

2.9

To assess the impact of exercise on brain morphology, function, connectivity, white matter microstructure, and cerebral blood flow, a magnetic resonance imaging (MRI) is completed at baseline and endpoint. A Siemens Prisma 3T scanner with a 64-channel head coil will be used to complete MRI scans. Structural imaging consisted of high-resolution three-dimensional (3D) anatomical sequences including a Magnetization-Prepared Rapid Acquisition with Gradient Echo (MPRAGE) T1-weighted sequence with navigator correction (sagittal orientation, 0.8 mm isotropic resolution, TE/TI/TR = 1.81–7.18/1000/2500 ms, field of view (FOV) 256 mm × 240 mm, 208 slices, GRAPPA acceleration factor = 2). An anatomical scout sequence was also acquired for positioning (sagittal orientation, 1.6 mm isotropic resolution, TE/TR = 1.37/3.15 ms, FOV 260 mm, 128 slices, GRAPPA acceleration factor = 3). Diffusion-weighted imaging (DWI) utilized a high-resolution multi-shell sequence with anterior-posterior (AP) and posterior-anterior (PA) phase encoding directions for distortion correction (1.5 mm isotropic resolution, TE/TR = 89.20/3230 ms, multiband acceleration factor = 4, FOV 210 mm, 92 slices, b-values of 0 and 3000 s/mm^2^, 98 gradient directions, monopolar diffusion scheme). Functional MRI included a resting-state Echo Planar Imaging (EPI) sequence (2.0 mm isotropic resolution, TE/TR = 37/800 ms, multiband acceleration factor = 8, FOV 208 mm, 72 slices, 600 measurements, PA phase encoding direction). Field mapping sequences for distortion correction were acquired with matching geometry (2.0 mm isotropic resolution, TE/TR = 66/8000 ms, FOV 208 mm, 72 slices) in both AP and PA phase encoding directions. Arterial spin labeling (ASL) perfusion imaging employed a pseudo-continuous ASL (pCASL) sequence with multiple post-labeling delays (2.5 × 2.5 × 3.0 mm resolution, TE/TR = 36.48/4100 ms, transversal orientation, FOV 240 mm, 42 slices, flip angle = 120°, fat saturation, post-labeling delays = 500, 1000, 1500, 2000, 2500 ms, 13 measurements total including calibration scans).Data will undergo quality control assessments for sequency accuracy (naming standards, correct number of volumes, correct sequence parameters). Then, data are converted to NIfTI format and structured per the Brain Imaging Data Structure (BIDS). Structural and functional data will then be preprocessed using fmriprep [74]. DWI data will be preprocessed using MRtrix3 [75]. ASL data will be preprocessed using ExploreASL [76]. A visual inspection of the data is done for quality control purposes to ensure preprocessing steps were completed without errors.

### Electroencephalography

2.10

An EMOTIV FLEX 2 Saline - 32 Channel Wireless EEG Head Cap System was used to assess the effects of exercise on changes in brain function. The electrode montage is based on the 10–20 international system [77,78]. 10 min of resting state electroencephalography (rs-EEG) will be conducted where participants will be instructed to focus on a fixation point in the middle of the screen for 5 min during the eyes open condition and will be instructed to have their eyes closed for 5 min during the eyes closed condition. Each participant will be positioned 41 cm from the screen to achieve homogeneity in rs-EEG collection. Data will be pre-processed using a custom MATLAB script. Data will undergo filtering, re-referencing to the average of all electrode sites, bad channel rejection, independent component analysis (ICA) deconstruction, eye-correction, ICA component removal, segment rejection, and interpolation. Post-processing will include a spectral power analysis using fast Fourier time-to-frequency domain transformation. Boundaries for the canonical frequency bands are as follows: delta (1–4hz), theta (4–8hz), alpha (8–13hz), beta (14–30hz), and gamma (31–45hz) [79].Power spectral metrics will also be input into a custom Python script including fitting oscillations one over f (FOOOF) [80]. This will be done to obtain aperiodic metrics of brain function.

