### Post study report and survey

2.17

After participants complete the study, they receive a post study report (Fig. 3) and feedback survey to fill out. The post-study report allows participants to receive feedback on their progress throughout the study. The cognition on the survey is TMT-B completion time. The balance is BESS total score. Fitness is CRF determined from Astrand-Rhyming test. Symptoms are the CIF total symptom score at baseline before the Astrand-Rhyming test. Brain function is alpha peak frequency from EEG. The feedback survey allows for the research team to receive feedback and make improvements to the study and future studies, as well as collecting data on reasons for low adherence and dropouts.

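### The EEG steps, as listed, take the average reference over all 32 sites before bad channels are rejected, which leaves 1/32 of each bad channel in every retained channel; minor, and cheap to correct

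*Protocol article*

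**What the plan says.** All of the preprocessing text is in section 2.10 (Electroencephalography) of the protocol article.

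- Equipment: "An EMOTIV FLEX 2 Saline - 32 Channel Wireless EEG Head Cap System was used".
- Recording: "10 min of resting state electroencephalography (rs-EEG) will be conducted", half with eyes open and half with eyes closed. Table 2 places EEG at baseline and at endpoint.
- First steps: "Data will undergo filtering, re-referencing to the average of all electrode sites, bad channel rejection".
- Remaining steps: "independent component analysis (ICA) deconstruction, eye-correction, ICA component removal, segment rejection, and interpolation".
- Outputs: "Post-processing will include a spectral power analysis using fast Fourier time-to-frequency domain transformation", in the bands "delta (1–4hz), theta (4–8hz), alpha (8–13hz), beta (14–30hz), and gamma (31–45hz" Hz), and a FOOOF fit, of which the article says: "This will be done to obtain aperiodic metrics of brain function".

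The average is described as covering every site. The section does not mention leaving bad channels out of it, a robust average, or a second average reference after rejection or interpolation.

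Section 2.17 uses one EEG measure in the participant report: "Brain function is alpha peak frequency from EEG".

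**The concern.** An average reference subtracts the mean of the contributing channels from each channel. If a faulty electrode is among them, part of its noise is subtracted from every good channel. Discarding the faulty channel later removes its own trace but not the part already copied elsewhere. Interpolation then rebuilds it from neighbours that carry the same term.

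The chosen outputs are sensitive to this. Resting EEG power is low at high frequencies, so a small broadband term can be a large fraction of beta and gamma power and can change a fitted aperiodic exponent. Both visits go through the pipeline, and the pilot is meant to give means and variances for a later trial. An avoidable processing error in either visit's data is therefore worth removing.

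**Working it through.** The article states no figure on this point, so there is none to reproduce.

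**Input from the document.** N = 32 channels; order of steps, band limits and outputs as in section 2.10.

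**Assumptions not in the document.** Number of bad channels m; their amplitude k, as a multiple of a good channel's SD; the spectrum of their noise; a 1/f^1.5 EEG background; a sampling rate of 256 Hz. ICA is not modelled, so every figure below is a pre-ICA figure.

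**Algebra.** With one bad channel b, retained channel i becomes x_i − c, where c = (sum of good channels + b)/32. The bad channel contributes −b/32 to every retained channel. For m independent bad channels, the added variance relative to a good channel is about m·k²/32².

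| k | m = 1 | m = 3 |
|---|---|---|
| 1 | 1/1024 = 0.1% | 0.3% |
| 3 | 9/1024 = 0.9% | 2.6% |
| 5 | 25/1024 = 2.4% | 7.3% |
| 10 | 100/1024 = 9.8% | 29% |
| 20 | 400/1024 = 39% | 117% |

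**Closed-form check on gamma, flat noise over 1–50 Hz.**

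1. The share of 1/f^1.5 power lying in 31–45 Hz is [2(1/√31 − 1/√45)] / [2(1 − 1/√50)] = 0.0611/1.717 = 0.0356.
2. At k = 10, the leaked noise in that band is 0.0977 × 14/49 = 0.0279, so gamma is multiplied by 1 + 0.0279/0.0356 = 1.78.
3. At k = 3, the leaked noise is 0.00879 × 14/49 = 0.0025, so gamma is multiplied by about 1.07.

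**Simulation.** 32 correlated channels, 300 s, 1/f^1.5 background with an alpha peak; log-log slope fitted over 2–45 Hz, leaving out 6–14 Hz. The listed order was compared with rejecting before averaging, which gave an exponent of 1.51.

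| Bad channels | Exponent, listed order | Band power |
|---|---|---|
| 1 white, k = 1 | 1.50 | gamma +1% |
| 1 white, k = 5 | 1.42 | gamma +24% |
| 1 white, k = 10 | 1.23 | beta +37%, gamma +94% |
| 1 white, k = 20 | 0.89 | gamma +367% |
| 3 white, k = 10 | 0.97 | gamma +271% |
| 1 slow drift (1/f²), k = 10 | 1.54 | delta +15%, gamma +3% |
| 1 slow drift (1/f²), k = 20 | 1.61 | delta +59% |

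Other simulation set-ups, with one white-noise channel at k = 10, gave exponents from 1.18 to 1.33 and gamma from 1.5 to 2.2 times. Noise with the same 1/f^1.5 shape as the EEG left the exponent at about 1.5. At k = 3 with white noise, the exponent was 1.48 against 1.51. Alpha peak frequency stayed at 9.75 Hz in all 16 cases tried (four noise spectra, 3 to 20 times SD).

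**Does the remedy work?** The term c is the same in every retained channel. Subtracting the mean of the retained channels therefore cancels it exactly: (x_i − c) − mean(x − c) = x_i − mean(x). In the simulation the result matched rejecting first to within 1e-13. The same holds after interpolation if the interpolation weights sum to one, because the rebuilt channel then carries the same −c.

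**The case against.** **The sentence may be an inventory.** It is a comma list with no sequencing word, whereas the MRI section marks order explicitly. The custom MATLAB script is not shown and may already use a robust or repeated reference, which an article can reasonably leave to a fuller document. It is right that silence about a second reference would not be a finding by itself. However, the list runs in natural processing order from filtering to interpolation and says the average covers every site. The step is stated, and read in the order given it is wrong. If the code differs, the text needs correcting.

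**ICA may remove the leak.** The leaked term is one time course with equal weight on all retained channels, a structure that ICA could isolate. Segment rejection could also remove intermittent bursts. This stands: the figures above describe the error before ICA, not the error in the final data.

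**Size and direction are assumed.** This also stands. A reader might infer that the pipeline flattens the aperiodic slope. That needs flat-spectrum noise, which the document does not describe; slow drift does the opposite, and noise shaped like EEG does neither.

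**Reach.** A reader might also infer that unequal numbers of bad electrodes at the two visits inflate the pilot's variance estimates, or that the participant report is wrong. The first is plausible, but no figure in the document supports it and it was not simulated. The second is not supported, since alpha peak frequency did not move. EEG is named in none of the aims in section 1.1; it falls under the secondary aim's brain-function metrics only by inference.

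**Conclusion.** The concern holds as a minor error in the stated order of steps. If section 2.10 is followed as written, each bad channel leaves minus 1/32 of its signal in every retained channel, and neither rejection nor interpolation undoes this.

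The consequence is conditional. It is negligible in practice for channels at 3 times normal SD or less, and can be material for band power and the aperiodic exponent from about 10 times SD. Its direction depends on the noise spectrum, and ICA may reduce it. These sizes rest on assumed bad-channel amplitudes, numbers and spectra. The documents do not support a claim that the trial's EEG results will be distorted in a known direction, that change-score variance is inflated, or that alpha peak frequency is affected. The primary feasibility aim is untouched.

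**What to change.** In section 2.10, state one of the following:

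- bad channels are detected and excluded before the average reference is computed; or
- the average reference is recomputed on the retained channels after rejection, or after interpolation.

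Apply the same script to every baseline and endpoint file, including any already processed. If the script already does this, correct the sentence to match it.

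The cost is a few lines of code and reprocessing of stored recordings. No new data are needed and no study procedure changes.

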### Psychosocial assessments

2.11

A battery of questionnaires are administered at baseline and endpoint including quality of life and lifestyle behaviors questionnaires (see Table 2). Additionally, pre-injury behaviors are of interest to see how engagement in healthy lifestyle behaviors pre-injury may contribute to recovery from mTBI. As such, we will administer a modified International Physical Activity Questionnaire (IPAQ), asking specifically about pre-injury physical activity engagement.

**Table 2 tbl2:** Study assessments and timeline.

	Phone Screen	Baseline (in person)	Randomization	Week 6	Week 12	Endpoint (in person)
Prescreening Questionnaire	X					
The Physical Activity Readiness Questionnaire (PAR-Q)	X					
Informed Consent		X				
Demographics		X				
The Ohio State University Traumatic Brain Injury Identification Method (OSU TBI-ID) Questionnaire		X				
Hopkins Verbal Learning Test (HVLT)		X				X
Patient-Reported Outcomes Measurement Information System (PROMIS)		X				X
Menstrual History Questionnaire [81]		X				
International Physical Activity Questionnaire (IPAQ)		X				
Pittsburg Sleep Quality Index (PSQI)		X				X
Verbal Fluency		X				X
Mediterranean Diet Adherence		X				
Trail Making Test (TMT) A and B		X				X
Magnetic Resonance Imaging		X				X
Electroencephalography		X				X
Balance Error Scoring System (BESS)		X				X
Cardiorespiratory Fitness Test		X				X
Actigraphy		X		X	X	

### Physical activity monitoring

2.12

Physical activity, sedentary time, and sleep metrics will be measured using an GT9X Link accelerometer (ActiGraph LLC, Pensacola, FL). An accelerometer is worn on the non-dominant wrist to improve compliance and allow for assessment of sleep characteristics. Time spent in physical activity, as well as time spent in light, moderate, and vigorous intensities are measured. Participants are also asked to complete a sleep log and record times when they remove and the device during each day (e.g., before and after taking shower). Actigraphs will be uploaded using ActiLife and preprocessed using R package *ggir* [82].

### Study assessments

2.13

See Table 2 for complete schedule of all study assessments.

### Intervention

2.14

All participants will engage in staff-led virtual exercise interventions three times a week for 30-min (5-min warm up, 20-min of aerobic/balance exercises, 5-min cooldown) for 12 weeks, making a total of 36 intervention sessions. Three sets of five exercises with modifications per each exercise have been developed for each intervention group (balance and aerobic) to help maintain engagement and allow intensity of the exercise to progress (see Table 3). Participants are seen individually for intervention sessions to ensure the research team can individualize exercise guidance and for safety monitoring All virtual sessions will be administered by two trained research staff members, one who leads the exercise session and one safety observer, monitoring safety. Heart rate (HR) will be monitored and recorded by hyperate4health (https://hyperate4health.netlify.app/), a proprietary open access platform and participants will be asked to rate their symptoms and exertion every 5 min. By collecting symptoms, HR using a Polar chest strap, and RPE every 5 min, we are directly targeting key limitations in other aerobic exercises studies done in TBI populations [18]. Aerobic sessions have a goal of reaching 20 min of aerobic exercise performed at 80 % of HR at symptom threshold. If this intensity increases symptoms by +3 on the symptom checklist, a 1-min break is taken, and the goal is reduced to 60 % of symptom threshold HR. If this intensity still exacerbates symptoms, another 1-min break is taken, and exercises will be done with a goal of 40 % of symptom threshold HR. Virtual aerobic exercises have been developed by an American College of Sport's Medicine certified Exercise Physiologist (JC) with experience delivering virtual aerobic interventions in older adults [83]. All participants are given a Polar HR strap and instructions on how to connect to HypeRate via Bluetooth to monitor their HR. Participants in the balance group are sent home with a foam pad to engage in non-aerobic physical activity like balance exercises. Each exercise is progressive in nature and includes modifications. All balance exercises were developed by a physical therapist (JM) and commonly used in clinical practice.

**Table 3 tbl3:** Intervention description.

Exercise description	Modification
Aerobic Version A	
Standing Twists w/Arm push	Normal, high arm, high arm with speed
Half Jacks	One arm, both arms, with jump
Imaginary Ball Slams	Normal, on toes, touch ground
Lateral Shuffles	Normal, Arms overhead, arms overhead with speed
Imaginary Kettlebell swings	Normal, Side steps, forward steps
Aerobic Version B	
Large step to back shuffle	Step, Leap, leap with arms overhead
Skaters	Normal. Touch ground, ground to overhead
Punching knees bents	Normal, jab cross/hook, jab cross/knee
Skiers	Small steps, large steps, high arms with steps
Elbow to knee	Elbow only, elbow to knee, add hop
Aerobic Version C	
Toe Taps	Hands on hips, high arms, high arms with speed
Standing dead bugs	Opposite arm/leg, overhead arm/opposite leg, both arms overhead
One leg diagonal step	Slight bent knee, arms to side, arms overhead
V-Steps	Normal, arms overhead with step, arms overhead always
Step overs	Normal, with arms pulling, arms overhead
Balance Version A	
Seated reach outside base of support	Normal, Foam Pad
Seated Wood Choppers	Normal, Foam Pad
Standing reach outside base of support	Normal, Foam Pad
Standing eyes closed	Normal, foam pad, narrow base of support
Standing eyes open on foam pad	Normal, narrow base of support, single leg
Balance Version B	
Seated marches	Normal, Foam Pad
Seated Crossbody Oblique Dips	Normal, Foam Pad
Standing Marches	Normal, Foam Pad
Tandem Stance	Eyes open, eyes closed
Clocks	Normal, foam pad
Balance Version C	
Seated cat cow	Normal, Foam Pad
Rotating knee taps	Normal, Foam Pad
Calf raises	Normal, Foam Pad
Drinking birds	Normal, Foam Pad
Tandem foot placement	Eyes open, eyes closed

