### Analysis plan

2.18

The goal of the pilot study is to complete 24 participants (12 in each group). Data will be checked for completeness and correctness using frequency distributions. Group differences at baseline will be examined for demographic factors, baseline symptoms, baseline estimated CRF, baseline balance, and baseline cognition to detect potential confounding factors. For the primary feasibility aim, we will report dropouts, adherence rates, retention rates, adverse events, and compliance. Statistical models to test for differences in outcomes over time between groups will be used but inferences will not be made based on p-values given the sample size was chosen based on feasibility and precision and variance around the mean difference. Therefore, all models will be reported as effect sizes with standard error of the means and 95 % confidence intervals around the mean.

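### The third step-down goal, 40% of raw symptom-threshold heart rate, is capped at about 56 to 69 bpm and is not a workable aerobic target

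*Protocol article*

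**What the plan says.** Section 2.7 of the protocol article describes the threshold test. It stops at a symptom rise of 3 or more, at 85% "of age-predicted maximum heart rate or RPE of 18 on the Borg scale", or at a contraindication. Its result sets the dose: "The heart rate at symptom threshold is recorded and used to prescribe aerobic exercise intensity for intervention sessions". Resting heart rate is measured at the same visit: "Baseline vital signs (heart rate, blood pressure) are recorded during seated rest".

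Section 2.14 sets the session goals. The first is stated as: "Aerobic sessions have a goal of reaching 20 min of aerobic exercise performed at 80 % of HR at symptom threshold". If symptoms rise by 3, "a 1-min break is taken, and the goal is reduced to 60 % of symptom threshold HR". Then: "If this intensity still exacerbates symptoms, another 1-min break is taken, and exercises will be done with a goal of" 40% of symptom-threshold heart rate. All three are plain percentages of the threshold heart rate. Resting heart rate does not enter them, and no floor is given.

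The exercises meant to meet these goals are in Table 3 (for example half jacks, lateral shuffles, skaters and step overs). None of the aerobic ones is listed as seated.

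**The concern.** A percentage of raw heart rate does not start from rest: zero effort corresponds to resting heart rate, not to 0 bpm. A small enough percentage therefore lands at or below rest, where no exercise can meet it. The test cap puts an upper limit on the reference heart rate, so one can check whether the lowest goal falls there for every eligible participant.

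If it does, staff at the third step must either let the participant rest or disregard the goal, and the article does not say which. Minutes near rest could then be counted as delivered aerobic exercise. That matters in a pilot meant to pass its dosing rule to a larger trial, and the step concerns the most symptomatic participants, for whom symptom-guided dosing is designed.

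**Working it through.** **Inputs from the article.** Session goals of 80%, 60% and 40% of threshold heart rate (section 2.14); test cap of 85% of age-predicted maximum (section 2.7); ages 18 to 55 (Table 1). The article gives no bpm figure for the goals, so there is none to reproduce.

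**Assumptions.** The formula for age-predicted maximum is not named; 220 - age is used, with others as a check. Resting heart rate is not given; 55 to 75 bpm is considered.

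**Step 1: ceiling of each goal** = fraction × 0.85 × (220 - age).

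| Age | Cap (bpm) | 80% goal | 60% goal | 40% goal |
|---|---|---|---|---|
| 18 | 0.85 × 202 = 171.7 | 137.4 | 103.0 | 68.7 |
| 35 | 0.85 × 185 = 157.2 | 125.8 | 94.3 | 62.9 |
| 55 | 0.85 × 165 = 140.2 | 112.2 | 84.1 | 56.1 |

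At the cap the 40% goal is 0.40 × 0.85 = 34% of age-predicted maximum.

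**Step 2: sensitivity.**
- With 208 - 0.7 × age, the 40% ceiling is 66.4 bpm (age 18) and 57.6 bpm (age 55). With 211 - 0.64 × age it is 67.8 and 59.8 bpm.
- If heart rate overshoots the cap by 5 bpm, the goal rises by 0.40 × 5 = 2 bpm.
- Even without the 85% cap, 40% of the full maximum is 0.40 × 202 = 80.8 bpm (age 18) and 0.40 × 165 = 66.0 bpm (age 55).

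**Step 3: thresholds below the cap.** At 120 bpm the goals are 96, 72 and 48 bpm. At 140 bpm they are 112, 84 and 56 bpm.

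**Step 4: comparison with rest.** The 40% goal equals rest when threshold = rest / 0.40.
- Rest 55: threshold 137.5 bpm, within the cap at every eligible age. At the cap the goal is 56.1 - 55 = 1.1 bpm (age 55) to 68.7 - 55 = 13.7 bpm (age 18) above rest.
- Rest 60: threshold 150 bpm, possible only up to age 220 - 150 / 0.85 = 43.5. At the cap the goal is 68.7 - 60 = 8.7 bpm above rest at age 18 and 60 - 56.1 = 3.9 bpm below it at age 55.
- Rest 70: threshold 175 bpm, above the cap at every eligible age.
- Rest 75: threshold 187.5 bpm, likewise out of reach.

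**Step 5: how much of a session is affected.** The active block is 20 min, with symptoms rated every 5 min. Suppose each session starts at 80% (the natural reading, though not explicit), both rises are caught at scheduled ratings, and the breaks fall inside the block. Then a double step-down uses 5 + 1 + 5 + 1 = 12 min and leaves 20 - 12 = 8 min at the 40% goal.

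**The case against.** The strongest reply is that the third step is a fallback, not the prescription. It needs a symptom rise at 80% and again at 60% of the heart rate recorded at threshold, and it governs only the remainder of that session. Sessions are individual, led by one staff member with a second observing, and monitoring is close: "By collecting symptoms, HR using a Polar chest strap, and RPE every" 5 min. The intensity actually reached can therefore be reported whatever the written goal says. This stands, and it limits the point to one step of one rule.

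A reader might infer more, in three ways that the article does not support.

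- **That these participants' aerobic sessions amount to rest, so that the contrast between arms is diluted by a calculable amount.** Time at 80% and 60% comes first, and the number who reach the third step is not documented, so no dilution can be computed. Nor are there heart-rate data to show that such a session is lighter than the balance arm's.
- **That the primary feasibility results are compromised.** Section 2.18 says: "For the primary feasibility aim, we will report dropouts, adherence rates, retention rates, adverse events, and compliance". It does not tie adherence or compliance to reaching a heart-rate goal. They may mean attendance or session completion, and those definitions may sit in a plan that is not shown.
- **That the other two goals fail as well.** The 80% goal is workable. The 60% goal, at most 84 to 103 bpm, approaches resting level only with low thresholds.

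It is also fair that resting level is an assumption here. With a resting rate of 55 bpm and a threshold near the cap, the goal lies 1 to 14 bpm above rest. That is still a very small margin for lateral shuffles or skaters.

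The reply does not remove the arithmetic. The goal is written as a number in the current text, so this is not detail that a condensed article leaves out. Figure 2 is not shown, but it concerns the test; the session goals are in section 2.14.

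**Conclusion.** The point holds for the 40% step alone. Its goal is at most about 56 to 69 bpm (ages 55 to 18, with 220 - age), and the other formulas tried give similar limits. At a resting heart rate of 60 bpm or more it is at most about 9 bpm above rest. It exceeds rest only for younger participants who combine a low resting rate with a threshold near the cap; at 70 bpm or more it is below rest for every eligible age. It is not a workable aerobic goal for the exercises listed.

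The consequence concerns dose and its reporting in sessions with two step-downs. It does not bear on sample size or error rates. The rule is worth correcting because it is stated, cannot be followed as exercise, and would otherwise pass to the next trial.

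**What to change.** Keep the 80% and 60% goals. Replace the 40% goal with symptom-limited light activity or recovery that carries no heart-rate target, or end the aerobic block if symptoms persist. Record those minutes separately and do not count them as aerobic exercise at the prescribed intensity.

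For sessions already delivered, report the minutes spent at each step and the session heart rate relative to the seated resting value recorded at baseline. Both heart rates are already collected. If the step in force was not logged, it can be approximated from the five-minute ratings.

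The cost is a wording change to the session instructions, and the reported aerobic dose may come out slightly lower.

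Raising the lowest goal to sit clearly above rest looks natural but is not advised. With a threshold of 140 bpm and a resting rate of 70 bpm, the 60% goal that has just provoked symptoms is 84 bpm, which leaves only 84 - 70 = 14 bpm in which to place another target.
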